## Procedures (template)

Individuals diagnosed with ischemic stroke will be sent to the rehabilitation center after discharge from the hospital. All individuals with ischemic stroke confirmed by a computed tomography (CT) or magnetic resonance imaging (MRI) scan will be invited to participate in the study. The patient, a family member, or guardian must sign an informed consent form. The individuals will then be evaluated for their clinical and neurological status. Individuals will be assessed using the National Institutes of Health Stroke Scale (NIHSS), the Barthel Index of ADL, and the mRS. The aerobic capacity will be evaluated by VO_2max_, functional capacity will be assessed by a 6-min walk test, nutritional status by electric bioimpedance, cardiologic examination by ecocardiography, and laboratory exams and the quality of life will be based on the European Quality of Life Scale. The tests will be performed by an investigator who is blinded to the treatment that the patient received before the first session and a week after the last session. After the clinical screening, they will be randomized into the following two groups: 1) control group (CG; 20 patients); 2) intervention group (IG; 20 patients) (Fig. 2).

**Fig. 2 Fig2:**
[figure not shown]
Template of recommended content for the schedule of enrolment, interventions, and assessments. *6MWT* 6-min walk test, *ABPM* ambulatory blood pressure monitoring, *BI* Barthel Index, *LDL* low-density lipoprotein, *HDL* high-density lipoprotein, *FPG* Fast plasma glucose test, to evaluate the glycemic control

## Data monitoring

Patients of both groups, CG and IG, will be evaluated initially and after 16 weeks of research, using the following procedures.

### Clinical evaluation

The clinical evaluation will include anamnesis and a general physical examination, recording demographics, morbidities, and medications in use.

### Physical assessment

The physical evaluation will consist of anthropometric measures and evaluation of the peripheral muscular strength.

### Evaluation of functional capacity

#### Aerobic capacity

A maximum stress test will be used to obtain VO_2max_, peak work rate, and anaerobic ventilatory threshold. The heart rate and resting blood pressure will be measured before and after the exercise. The stress test will be based on a modified Bruce protocol that uses a time-dependent slope [31]. The protocol will be based on the study by Tang et al. [32], which used 5, 10, or 15-watt work rates for a total test duration of between 8 and 10 min.

#### Six-minute walk test

The 6-min walk test establishes functional fitness of gait through performance and physical resistance. The test measures the maximum distance reached along a course of 30 m in 6 min. The expected distance to be reached by the patient will be calculated based on age, sex, weight, and height [33, 34]. Equipment required for the test include a stopwatch, cones for circuit delimitation, sphygmomanometer, stethoscope, and pulse oximeter. According to the protocol proposed by the American Thoracic Society guidelines, the evaluator should not walk with the patient, but may walk behind the patient if necessary to carry the oxygen source or in case the patient loses balance. During the test, encouraging (standardized) phrases should be used over time. Vital signs are checked at the beginning and end of the test [35].

### Neurological and functional evaluation

#### National Institutes of Health Stroke Scale

The NIHSS is an assessment to quantify the neurological deficits as well as the severity of the stroke. The assessment can be performed by both medical staff and health professionals with proven training and certification [1].

#### Modified Rankin Scale

The mRS is to assess the degree of independence and determine if patients can care for themselves during ADL [1]. The scale ranges from 0 to 6, and the greater the score, the lower the functional capacity.

#### Barthel Index

The Barthel Index will be used to measure the functional independence of individuals in 10 ADL, and the score varies from 0 to 100. A score above 95 indicates that an individual is independent in all ADL [1].

### Nutritional assessment

#### Electrical bioimpedance

Electrical bioimpedance is a non-invasive, practical, and reproducible method for evaluation of the body composition and distribution of intra- and extracellular fluids of a patient [36, 37]. Based on the principle that different body tissues offer different resistance levels to the passage of an electric current, electrodes are placed at the tips of the thumbs, middle fingers, and heels for passing a low intensity electrical current. The amount of resistance offered helps in assessing tissue differentiation and distribution of body fat [37]. It also provides data on body mass index, which is an anthropometric indicator to establish nutritional status and measure abdominal circumference as an indicator of chronic diseases.

### Cardiological evaluation

#### Ambulatory blood pressure monitoring

Ambulatory blood pressure monitoring is a diagnostic method that monitors 24-h changes in blood pressure, during both wakefulness and sleep, and its effect on the patient. It allows a better understanding of systemic arterial hypertension for diagnosis, prognosis, and appropriate treatment [38]. The device will be programmed for readings at 20-min intervals during wakefulness and 30 min during sleep, with a minimum of 14 readings when awake and seven during sleep. The period of vigilance will be between 7 am and 10 pm. At least two test measures will be performed before the patient is discharged. The readings will be considered valid if there is a minimum of 24 h of recording and a minimum number of valid measures per hour (three during the waking hours and two during sleep). The following parameters will be analyzed: systolic mean arterial pressure, diastolic and 24 h pulse pressures (wakefulness and sleep), and magnitude of the nocturnal decrease in systolic, diastolic, and pulse pressures [39].

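### The ABPM per-hour validity minimum equals the programmed reading rate, so one failed reading invalidates a recording and the 14/7 minimum has no function

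*Protocol article*

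**What the plan says.** All the relevant text is in the section "programmed for readings at 20-min intervals during wakefulness and 30 min during sleep" belongs to, Ambulatory blood pressure monitoring in the protocol article. That phrase sets the device schedule, and its sentence continues "with a minimum of 14 readings when awake and seven during sleep". The waking window is then fixed: "The period of vigilance will be between 7 am and 10 pm". Acceptance is defined separately: "The readings will be considered valid if there is a minimum of 24 h of recording" together with "a minimum number of valid measures per hour (three during the waking hours and two during sleep").

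The section lists 24 h, waking and sleeping pressures and the size of the night-time fall as the parameters to be analysed. The closing paragraph of the Background names several of these as variables in the association aim. Secondary outcome measures lists cardiologic evaluation, the heading under which ABPM falls. Data monitoring has both groups assessed at baseline and after 16 weeks, so each patient should contribute two recordings.

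**The concern.** An acceptance threshold for an automated device normally sits below the number of readings attempted, because some cuff inflations fail. Here the hourly threshold equals the number attempted, so the rule has no tolerance. The section also gives a much lower total minimum and does not explain how the two relate.

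Two things are at stake. First, applied as written, the hourly rule could remove recordings that lack only one or two readings, and the recordings that remain may be a selected subset. Second, many recordings would be acceptable by the 14/7 totals and invalid by the hourly rule. Unless one rule is fixed beforehand, the ABPM analysis set could depend on a choice made after the data are available.

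**Working it through.** **Inputs from the ABPM section.** Interval 20 min awake and 30 min asleep; waking window 7 am to 10 pm, so 15 h awake and 24 − 15 = 9 h asleep; minimum recording 24 h; hourly minimum three awake and two asleep; total minimum 14 awake and seven asleep.

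**Inputs not in the document (assumptions).** Reading-failure rate f, shown from 1% to 10%; failures independent with a common rate; no automatic repeat of a failed reading.

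**Step 1: readings programmed.** Awake 15 × 60/20 = 45; asleep 9 × 60/30 = 18; total 63.

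**Step 2: readings required by the hourly rule.** Awake 15 × 3 = 45; asleep 9 × 2 = 18; total 63. The requirement is 63 of 63. Reading the rule as an hourly average changes nothing, because the totals needed are still 45 and 18.

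**Step 3: the 14/7 minimum on the same scale.** 14/45 = 31% awake and 7/18 = 39% asleep. Per hour this is 14/15 = 0.93 and 7/9 = 0.78, below one reading per hour. Any recording that meets the hourly rule has 45 and 18 readings and so meets 14/7 automatically. The reverse fails: a recording with at least 14 awake and seven asleep valid readings, but fewer than 63 in all, meets the totals and fails the hourly rule.

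**Step 4: share of recordings passing.** Hourly rule: (1 − f)^63. Valid at both visits, treating the visits as independent: the square of that. If 14/7 were the acceptance rule: P(at least 14 of 45) × P(at least 7 of 18), binomial with success probability 1 − f.

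| Failure rate f | Hourly rule, one recording | Hourly rule, both visits | 14/7 totals, one recording |
|---|---|---|---|
| 1% | 53.1% | 28.2% | over 99.9% |
| 2% | 28.0% | 7.8% | over 99.9% |
| 5% | 4.0% | 0.2% | over 99.9% |
| 10% | 0.1% | about 0% | over 99.9% |

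**Step 5: where the loss becomes large.** Half of single recordings are lost when (1 − f)^63 = 0.5, so 1 − f = 0.989 and f is about 1.1%. Losing 95% needs 1 − f = 0.05^(1/63) = 0.954, so f is about 4.6%. At f = 0.1% the loss is only 6.1%.

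**Step 6: sensitivity to sleep length.** With 8 h or 7 h asleep the programmed total is 64 or 65, and the share passing at 1% failure is 52.6% or 52.0%. The waking window hardly matters.

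**The case against.** The strongest reply concerns the consequence, not the count.

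- **Size of the loss.** A reader might infer that the rule discards almost all recordings. The document does not support that, because it gives no failure rate. That reading needs about 5% failure or more; at 1%, slightly more than half of recordings pass. This part of the objection stands.
- **The model leans towards loss.** (1 − f)^63 is convex in f, so if failure rates differ between patients, more recordings pass than at the same average rate. Failures clustered within a few recordings act the same way. Automatic repeats, on which the protocol is silent, would also help. Squaring for two visits ignores correlation within a patient, which would raise the share of complete pairs. All of this stands, and the table should be read with it in mind.
- **The minima are not contradictory.** A reader might say that the two rules contradict each other. Strictly they are nested: meeting the hourly rule meets 14/7. The 14/7 clause also sits in the device-programming sentence, and only the later sentence speaks of validity. That weakens the argument about choosing an analysis set afterwards, but does not remove it. The programmed schedule already yields 45 and 18 readings, so a minimum of 14 and seven makes little sense except as some kind of acceptance limit.
- **Intended rule.** A reader might infer that 14/7 is the validity rule the authors meant. The text does not call those readings valid and does not settle this.
- **Article format.** How an invalid recording is handled may be left to a fuller document, and its absence is no fault. But both minima are stated here, and how they fit together is a matter of the stated text.

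**Conclusion.** The point holds in a limited form. It is certain from the document that the hourly minimum equals the programmed rate, that 63 of 63 readings must succeed on the stated schedule when a failed reading is not repeated, and that the 14/7 minimum then does no work. None of this depends on an assumed failure rate.

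The size of the loss is conditional. Under independent failures at a common rate and no repeats, it runs from about 47% of recordings at 1% failure to 99.9% at 10%, and is heavier for before-after pairs. Clustering or repeats would bring these figures down. Near-total loss is one end of that range and is not established.

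The effect is confined to the ABPM part of the secondary cardiologic evaluation and to the association aim. Neither primary endpoint nor the sample size calculation uses ABPM. It is a correction worth making, but it does not threaten the trial's main comparison.

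**What to change.** Replace the two minima with one data-validity rule that tolerates some failed readings. Either option would do:

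- the 14 awake and seven asleep totals, stated explicitly as valid readings; or
- a per-hour minimum set below the programmed rate. As an illustration, at least two valid readings per waking hour and one per sleeping hour would pass with probability [P(at least 2 of 3)]^15 × [P(at least 1 of 2)]^9. Under the same assumptions that is 99.5% at 1% failure, 97.9% at 2%, 87.7% at 5% and 59.7% at 10%.

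The document does not decide between them, so the choice belongs to the investigators. The text should also say whether the 24 h recording requirement stays, and that the same rule applies at both visits. The rule should be fixed before the data are seen.

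The cost is a sentence or two of text, with no added procedure. The downside is that some retained recordings will have fewer readings, including at night. Under the 14/7 totals a recording could enter with as few as seven night readings, so its nocturnal decrease would be estimated less precisely. A reduced hourly minimum guards better against long gaps but rejects more recordings when failures are frequent.

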#### Doppler echocardiographic evaluation

The Doppler echocardiographic evaluations will be performed by a single examiner using a Vivid S6 (General Electric Medical Systems, Israel) with multi-frequency ultrasonic transducer 2.0–3.5 MHz. During the procedure, patients will remain in a left lateral decubitus position, with the left upper limb slightly flexed under the head. An electrocardiographic shunt will be continuously monitored.

The images will be obtained and analyzed following the recommendations of the American Society of Echocardiography [40, 41].

##### Morphometric variables

Maximum left atrium diameter (LA, cm)Left atrial volume (LAV, mL), obtained by the Simpson method in two longitudinal planes, four and two chambersLeft ventricular diastolic and systolic diameters of the left ventricle (LV, mm): LVDD and LVSD, respectivelyInterventricular septum diastolic thickness (IVSDT) and posterior wall diastolic thickness (PWDT) of the LV (mm): IVSDT and PWDT, respectivelyRelative thickness of the LV (LVRT) = (2 × PWDT)/LVDDLeft ventricular mass (LVM, g) = 0.8 × {1.04 × [(IVSDT + PWDT + LVDD)^3^ − LVDD^3^]} + 0.6LVM index (LVMI, g/m^2.7^) = LVM/Height^2.7^ where LVMI is LV mass indexed to height.

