### Primary outcome measures

The primary endpoint will be measured as functional capacity following a 6-min walk test (delta maxVO_2_) and morphofunctional echocardiographic variables (indexed left ventricular mass) before and after the intervention.

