## Sample size estimation

The sample size was calculated to match primary outcome with sample size estimation.

According to Framingham data [47], an increase of 20 g/m^2.7^ in left ventricular mass index presents a hazard ratio to hard end points of about 1.5; in this study the standard deviation was 30 g/m^2.7^. To detect these clinically significant differences between groups, with a fixed alpha error of 0.05 and beta error of 0.20, 37 patients per group will be needed.

According to the cohort of Presher et al. [48], an increase of 66 m in the 6-min walking test discriminates survivors from non- survivors among heart failure patients; in that study the standard deviation was 90 m. To detect these clinically significant differences between groups, with a fixed alpha error of 0.05 and beta error of 0.20, 31 patients per group will be needed.

Therefore, we will study 40 patients per group to detect these differences properly.

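### The LV mass formula behind the indexed LV mass primary endpoint takes inputs defined in mm, but its constants give grams only with cm, so as written the endpoint is about 1000 times too large

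*Protocol article*

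**What the plan says.** The primary endpoint of the protocol article (Primary outcome measures, and the Abstract) names functional capacity together with "morphofunctional echocardiographic variables (indexed left ventricular mass) before and after the intervention".

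The only operational definition of indexed LV mass is under Morphometric variables. There:

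- LV diastolic diameter (LVDD) is given in mm.
- Septal and posterior wall thickness (IVSDT, PWDT) are also in mm: "posterior wall diastolic thickness (PWDT) of the LV (mm".
- LV mass, labelled in g, is 0.8 × {1.04 × [(IVSDT + PWDT + LVDD)³ − LVDD³]} + 0.6.
- The index, labelled in g/m^2.7, is "LVM/Height^2.7^ where LVMI is LV mass indexed to height".

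No conversion of the LV dimensions to cm appears there or elsewhere in the echocardiography text.

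Sample size estimation works on the same index. It plans on "an increase of 20 g/m^2.7^ in left ventricular mass index" and adds that "in this study the standard deviation was 30 g/m^2.7".

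**The concern.** The units of the inputs and of the output cannot both hold with these constants. The lengths are cubed, so a tenfold change of unit becomes a thousandfold change in the result. The factor 1.04 acts as a density in grams per cubic centimetre, so the bracket has to be in cm³ for the answer to be in grams.

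What is at stake is the reported scale of a primary endpoint. If the definition is followed literally, every LV mass index, every change from baseline and every between-group difference is inflated by roughly three orders of magnitude. None of them could be set against the planning difference or SD. Relative wall thickness and the percentage change in ventricular diameter are ratios of lengths, so they would look normal and would not reveal the slip.

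**Working it through.** **The plan's own figure first.** The article gives no worked LV mass. Its only figure derived on the index scale is the sample size: "with a fixed alpha error of 0.05 and beta error of 0.20, 37 patients per group will be needed". With a difference of 20, SD of 30, power 0.80 and alpha 0.05 (taken as two-sided, since the article does not say):

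- Normal approximation: n = 2 × (1.960 + 0.842)² × (30/20)² = 35.3, rounded up to 36 per group.
- t-test version: 36.3, rounded up to 37 per group.

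The stated 37 is reproduced. It rests on the difference and SD quoted from a cited study, so it does not depend on the formula's units.

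**One heart, two units.** The article gives no dimensions, so these are assumptions: IVSDT = PWDT = 10 mm, LVDD = 48 mm, height 1.65 m. Then 1.65^2.7 = 3.8655 and 0.8 × 1.04 = 0.832.

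- In mm, as written: 0.832 × (68³ − 48³) + 0.6 = 0.832 × (314,432 − 110,592) + 0.6 = 169,595 g. Divided by 3.8655, this is about 43,900 g/m^2.7.
- In cm: 0.832 × (6.8³ − 4.8³) + 0.6 = 0.832 × 203.84 + 0.6 = 170.2 g. Divided by 3.8655, this is 44.0 g/m^2.7.
- Ratio of the two LV masses: 169,595 / 170.2 ≈ 996.

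The cubic term scales by exactly 1000. The added 0.6 does not scale, so the total falls slightly short of 1000.

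**Range.** Other assumed hearts (septum/posterior wall/LVDD), at 1.65 m:

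| Dimensions, mm | LVM from mm, g | LVM from cm, g | Ratio | Index from mm | Index from cm |
|---|---|---|---|---|---|
| 8/8/42 | 100,693 | 101.3 | 994 | 26,049 | 26.2 |
| 10/10/50 | 181,377 | 182.0 | 997 | 46,922 | 47.1 |
| 14/14/58 | 366,866 | 367.5 | 998 | 94,908 | 95.1 |

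Over heights of 1.55 to 1.75 m the cm version runs from 22.4 to 112.5 g/m^2.7, the scale on which 20 and 30 g/m^2.7 make sense. The mm version runs from about 22,200 to 112,400 g/m^2.7, and implies left ventricles of 100 to 367 kg.

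**Effect on the tests if every record is computed in mm.** Write C for the cubic term (with its constants) in cm and h for height.

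- Correct index: (C + 0.6)/h^2.7. Index as written: (1000C + 0.6)/h^2.7.
- Within-patient change: height is unchanged, so the 0.6 cancels and the change is exactly 1000 times the correct one. A paired t-test, or a t-test or Mann-Whitney test on changes, gives the same p-value.
- Single time point: index as written = 1000 × (correct index) − 599.4/h^2.7. On the correct scale the offset is 0.5994/h^2.7, which is 0.18 g/m^2.7 at 1.55 m and 0.13 g/m^2.7 at 1.75 m. That spread of about 0.05 is negligible beside an SD of 30.
- Reported effects: a true difference in change of 20 g/m^2.7 would appear as 20,000 g/m^2.7.

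**The case against.** The strongest reply is that the bracketed mm are reporting units in a list of variables, that conversion is done elsewhere, and that a condensed article need not spell it out. This may describe what will happen in practice. It does not rescue the text: the units are attached to the very symbols the formula uses, and the article states both sides of the conflict, so this is not merely a detail left to another document. The reference to echocardiography society recommendations covers how images are obtained and analysed, and does not alter the explicit definition that follows.

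The second reply is that the error would reveal itself. That largely stands. A 170 kg ventricle would be noticed, and the output labels and the planning figures both point to the intended scale.

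Two stronger readings are tempting, and neither is supported.

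- A reader might infer that some records will hold cm and others mm, so that individual patients' changes would be wrong by a factor of about 1000. All three inputs to the formula are defined in mm. The dimension given in cm, left atrial diameter, does not enter LV mass. The section Doppler echocardiographic evaluation specifies a single examiner and a single named machine. Nothing in the article points to mixed recording.
- A reader might infer that the primary comparison or the sample size is invalid. A uniform slip leaves tests on change with identical p-values, and 37 per group is reproduced without the formula.

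**Conclusion.** The definition is wrong as written. LVDD, IVSDT and PWDT are in mm, the formula needs cm, and no conversion is stated. Followed literally, LV mass and its index come out about 1000 times too large: exactly 1000 for the cubic term, and 994 to 998 for the total over the hearts tried. The result does not fit the article's own planning scale of 20 and 30 g/m^2.7.

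The consequence is limited. Reported values and effect sizes would be wrong. The p-values of the planned tests would not change materially, and the sample size and the unit-free ratios are unaffected. It deserves correction because it is the stated rule for a primary endpoint and costs almost nothing to put right.

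The example values rest on assumed heart dimensions and heights. The factor of about 1000 does not depend on that choice. The statement about p-values assumes that the slip is uniform across patients and visits and that each patient's height is the same at both visits.

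**What to change.** Under Morphometric variables, add one clause: LVDD, IVSDT and PWDT enter the LV mass formula in cm (mm/10), and height enters the index in m. Equivalently, keep mm and divide the cubed term by 1000 before adding 0.6: 0.8 × 1.04 × [(IVSDT + PWDT + LVDD)³ − LVDD³]/1000 + 0.6.

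The cost is one line of text. No measurement, visit, sample size or test changes.
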